**Methods:**

This is a pilot, nonrandomized, pragmatic, repeated measures, mixed methods trial. We will recruit 32 participants diagnosed with lung or esophageal cancer and are scheduled to undergo surgical resection into the prehabilitation program, with 32 additional participants who decline participation to act as a control group. Participants who agree will then go through an 8-week tailored prehabilitation program (in person or virtual), covering movement, nutrition, stress management, nutrition, goal setting, and smoking cessation. They will complete 6 sessions prior to surgery and then have 4 sessions, 1×/week following surgery. Following the completion of the program, they will have 3 booster sessions via phone or Zoom (Zoom Video Communications). The primary outcome is feasibility: (1) recruitment feasibility—recruitment rate (the number of participants referred per month), enrollment rate (the number of enrolled participants divided by the number of referred participants), reasons for declining, and prehabilitation window (time between consent and surgery); and (2) intervention feasibility—adherence to the movement intervention, attrition, safety, study completion rate, and adverse events. Secondary outcomes include measures of preliminary effectiveness including patient-reported outcomes, such as well-being, fatigue, and functional measures. All measures will be assessed before, during, and after the prehabilitation program.

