Given the complexity of the health care system, pragmatic trials are important methodological tools to assess internal validity and improve current practice under real-world conditions [15]. Concurrently, using community resources is imperative to keep people active in their community and create sustainable programming. Practice-based evidence is an emerging field that strives to ensure research is applicable to real-world settings [16,17]. Practice-based evidence is derived from implementation science research methods, which assess effective intervention in real-world settings and provide insights into the system’s capacity and preparatory needs for dissemination and scalability [18]. The purpose of Boosting Recovery and Activity Through Early Wellness (BREATHE WELL) is to explore the feasibility, implementation, and preliminary effectiveness of a clinically integrated, community-based prehabilitation health coaching program, including nutrition, smoking cessation, sleep hygiene, and movement for individuals scheduled to undergo surgery for lung or esophageal cancer. Central to our research endeavor is the driving question: “How can a clinically integrated, community-based prehabilitation program be successfully implemented in the community, and can it lead to improved functional outcomes in patients undergoing surgery for lung or esophageal cancer?” This overarching question provides the study with its core focus and serves as a guiding force throughout the research process. The aim of this study is to investigate the implementation, feasibility, and effectiveness of BREATHE WELL, a community-based prehabilitation health coaching program specially designed for individuals scheduled to undergo surgery to address lung or esophageal cancer.

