### Outcome Measures

Feasibility (primary outcome) will include (1) recruitment feasibility—recruitment rate (the number of participants referred per month), enrollment rate (the number of enrolled participants divided by the number of referred participants), reasons for declining, and prehabilitation window (time between consent and surgery); and (2) intervention feasibility (adherence to the movement intervention, attrition, safety, study completion rate, and adverse events). The feasibility target for recruitment is a 25% enrollment rate. The feasibility target for adherence is 70% or more, measured by attendance to movement sessions with the qualified exercise professional. The feasibility target for attrition is 20% or less [22]. A timeline of feasibility measures is available in Table 3.

**Table 3 table3:** Timeline of program measures^a^.

		T0 (baseline)	T1 (before operation)	Surgery	T2 (after operation; weeks 4-6)		T3 (long-term follow-up; week 32)	

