### Statistical Analyses

The statistical analysis for this trial will be conducted with R (R Foundation for Statistical Computing). Participant characteristics will be summarized using descriptive statistics (mean, SD, frequency, and percentage). We will report on reasons for exclusion, attrition, and adverse events with frequency and percentages for each group. Safety will be determined by examining the total number of adverse events that occur over the duration of the program. Adherence to movement sessions will be summarized as a percentage (the number of movement sessions attended divided by the number of available movement sessions).

Baseline demographic and disease-related variables will be compared between prehabilitation and data-only participants using 1-way ANOVA for continuous variables and a chi-square test for categorical variables. The effectiveness analysis will include a linear mixed model to assess the difference in physical fitness and PROs from baseline (T0) to the preoperative (T1), postoperative (T2), 4-6 weeks postoperative (T3), and 32-week long-term follow-up (PROs only) time points, where the time point is the fixed effect and the individual participant is the random effect. A sensitivity analysis will be performed adjusting for sex, surgical type, and age. Linear mixed effect models will also be used to determine between-group differences. An α of .05 will be considered statistically significant. Point estimates and 95% CIs will be calculated for changes in the physical function and PROs at each timepoint and will also be used to provide important information for future sample size calculations. A Poisson regression will be used to estimate differences between groups for postoperative outcomes (ie, length of hospital stays, postoperative complications, return to emergency department, and mortality). Missing outcome data will be imputed using multiple imputation effects. Conclusions will be drawn using comparisons of each time point relative to the baseline.

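### Effectiveness is a preliminary, unpowered aim, yet the plan applies an unadjusted .05 to every outcome, visit and group contrast and draws conclusions from change against baseline

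*Protocol article*

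**What the plan says.** The protocol article's Statistical Analyses section sets out several analyses under one threshold.

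- **Within-group change:** "The effectiveness analysis will include a linear mixed model to assess the difference in physical fitness and PROs from baseline (T0") to each later visit, with time point as the fixed effect and participant as the random effect.
- **Between-group contrasts:** "Linear mixed effect models will also be used to determine between-group differences". Four postoperative outcomes (length of stay, complications, emergency return, mortality) are compared by Poisson regression.
- **Threshold:** "An α of .05 will be considered statistically significant". No adjustment or order of testing is given, and no effectiveness comparison is singled out.
- **Rule for conclusions:** "Conclusions will be drawn using comparisons of each time point relative to the baseline".

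The same section promises point estimates and 95% CIs for physical function and patient-reported outcomes (PROs), to help plan later sample sizes.

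The status of effectiveness is clear in the abstract: "Secondary outcomes include measures of preliminary effectiveness including patient-reported outcomes, such as well-being, fatigue, and functional measures". Feasibility is primary and is judged against descriptive targets. The Introduction nevertheless asks of the program, "can it lead to improved functional outcomes in patients undergoing surgery for lung or esophageal cancer".

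**The concern.** The threshold and the closing sentence together make every outcome at every visit a possible basis for an effectiveness statement. Two separate problems follow.

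1. **Chance.** With many tests at .05, some will probably or quite possibly cross the line when nothing has changed. A pilot report that picks out those results would present noise as preliminary effectiveness.
2. **Wrong comparison.** Change from baseline in people who have had a lung or esophageal resection mixes any program effect with the effects of surgery and recovery. A significant change, in either direction, does not isolate the program.

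At stake are the wording of the effectiveness conclusions and the reading of the estimates meant for the next trial. The feasibility result does not depend on this.

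**Working it through.** **Is any effectiveness test powered?** The Participants section gives 10 surgical patients per month, 16 months, 25% enrollment and 20% attrition: 10 × 16 × 0.25 × (1 − 0.20) = 32. This reproduces the program-group size exactly. No effect size, SD or power enters. The plan's only error-rate figure is the per-test .05, taken here as two-sided to match the 95% CIs.

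**How many tests?** The document does not fix the number. Counting by the visits in Table 3:

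| Block | Tests |
|---|---|
| Within group, 3 fitness tests (sit-to-stand, stair climb, grip) × 2 visits | 6 |
| Within group, 2 PROs × 3 visits | 6 |
| Between groups, 3 fitness tests × 2 visits | 6 |
| Between groups, postoperative outcomes | 4 |
| **Total** | **22** |

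The between-group part is 6 + 4 = 10. Between-group PRO tests are left out because control data are drawn from clinical records under a consent waiver. Pulmonary measures and the adjusted sensitivity analyses are also left out.

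The visit list is itself unsettled. Table 3 has "T2 (after operation; weeks 4-6") with T3 at week 32. The analysis section has a separate postoperative T2, then "4-6 weeks postoperative (T3), and 32-week long-term follow-up (PROs only) time points". Its list gives 3 × 3 + 2 × 4 = 17 within-group contrasts, against 12 by Table 3.

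**Chance of at least one p<.05 if every true change and difference is zero.** For k independent tests this is 1 − 0.95^k:

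- k = 10: 1 − 0.95^10 = 40.1%
- k = 22: 1 − 0.95^22 = 67.6%

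The tests are in fact correlated. I simulated normal test statistics, counted any |z| > 1.96, and let the between-group statistics share the program group's data with the within-group ones. The document gives no correlations, so these are assumed:

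| Correlation between outcomes / visits | 10 between-group tests | All 22 tests |
|---|---|---|
| 0.2 / 0.5 | 38% | 60% |
| 0.5 / 0.5 | 34% | 53-54% |
| 0.5 / 0.7 | 33% | 51% |
| 0.7 / 0.7 | 29% | 43-44% |

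The working ranges are therefore about 29-40% for 10 tests and 43-68% for 22.

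**Effect of surgery alone on one within-group test.** For a two-sided one-sample t test at .05 with n = 32, and a mean shift from surgery and recovery of d SDs of change (assumed), the noncentrality is d√32:

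- d = 0.3: significant 38% of the time
- d = 0.5: significant 78% of the time

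These results would reflect a real change that the program did not cause. Tightening alpha makes them rarer but leaves them just as uninformative about the program.

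**The case against.** The strongest reply is that multiplicity rules and the choice of a key secondary comparison commonly sit in a statistical analysis plan, which is not shown, and that this is a condensed article on a feasibility pilot. The alpha sentence is conventional. Nothing in the document says that one significant test proves effectiveness, and estimates with 95% CIs are already planned. Much of this stands: the absence of a multiplicity rule is not the point, and the severity is limited. What remains is what the article does state, namely a significance threshold for an unpowered preliminary aim and a rule that bases conclusions on change from baseline. An analysis plan could add detail, but both statements would still need correcting.

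A reader might go further and infer that a false finding is more likely than not when the program does nothing. The documents do not support that:

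- A rule that any p<.05 means the program works is not in the plan.
- Twelve of the 22 contrasts are within-group, and an inert program does not imply zero change after surgery. For the between-group tests, which do compare program with no program, the figure stays at or below about 40%.
- Neither the count nor the correlations are fixed. At 0.7/0.7 even the 22 tests fall below half.
- The 10-test count assumes controls have sit-to-stand data, which the routine assessment under Enrollment and Assessment does not list. Without it there are 8 tests: 1 − 0.95^8 = 33.7% if independent.

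Naming one key between-group test at .05 is also debatable. It would put a formal test on an unpowered comparison with people who chose to decline, and would not remove that selection bias.

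**Conclusion.** The point holds in limited form. The stated threshold and rule for conclusions do not fit a secondary, preliminary and unpowered aim. With no true change or difference, at least one p<.05 would occur about 29-40% of the time across the 10 between-group tests and about 43-68% across all 22, against 5% for one test. These figures rest on Table 3's visits, three fitness tests being available in controls, two-sided tests, and assumed correlations from zero to 0.7. They measure chance only. Confounding by surgery and recovery in the within-group tests, and by self-selection in the between-group tests, comes on top and is not cured by multiplicity control. The change should be made, but the primary outcome is unaffected.

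**What to change.** Amend the Statistical Analyses section:

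1. Remove the alpha sentence as it applies to effectiveness outcomes.
2. Replace the closing sentence with one stating that all effectiveness results are exploratory, reported as point estimates with 95% CIs, without significance labels, and that no conclusion about effectiveness will be drawn from change against baseline.
3. Give between-group estimates wherever both groups have data, and extend the CIs to the four postoperative outcomes, since they are now promised only for physical function and PROs.
4. Reconcile the visit labels with Table 3, so that it is clear which estimates will be reported.

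This costs a few sentences and no new data. The Results section reports only 2 program participants enrolled at the time of writing, so the change could be made early. The downside is that no effectiveness result in this pilot could be called significant.

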### Participants

Based on a monthly surgical volume of 10 patients per month to the referring surgeon, assuming an enrollment rate of 25% while accounting for 20% attrition within a 16-month recruitment window, we will seek to recruit 64 participants (aged 18 years and older) diagnosed with lung or esophageal cancer (32 in the program and 32 who decline). This is based on the number of surgical candidates that the current surgeon sees in a 2-year period. Participants will be identified based on the following inclusion criteria: (1) confirmed diagnosis of lung or esophageal cancer; (2) treatment plan includes surgery (at least 2 weeks from the time of consent) [20]; (3) fluent in English; and (4) surgical oncologist approval. Exclusion criteria include (1) unstable or symptomatic cardiac disease, musculoskeletal injury, or comorbid disease that precludes the ability to safely engage in physical activity or (2) significant cognitive limitations.

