The participants will be interviewed prior to the commencement of the program to better understand their perception of prehabilitation health coaching and to better understand their history with movement and healthy lifestyle behaviors. This will include questions that are based on past behaviors and future goals. This interview will be audio recorded and transcribed verbatim. A content analysis will be done using the Behavior Change Wheel and Theoretical Domains Frameworks [26,27]. This will aid in better understanding the behavior and barriers or facilitators to engage in the behavior. For sustained behavior change, participants need to have the Capability, Opportunity, and Motivation to perform the behavior [27]. Participants will also be interviewed at the end of the program to better understand their satisfaction with the program. This will also aid in understanding participants’ perceptions of where they are regarding long-term behavior change. Postprogram interviews will be conducted to better understand their perspective on the program and how or if they found the program beneficial; these interviews will probe the understanding of sustained health behavior change and program satisfaction.

Postoperative outcomes include length of hospital stay and postoperative complications. The severity of complications will be graded according to the Clavien-Dindo classification [28,29]. Return to the emergency department within 90 days after the operation and 90-day mortality will also be assessed.

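### One Poisson regression is named for stay, complications, emergency department return and mortality without matching model or variance to outcome type

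*Protocol article*

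**What the plan says.** The Statistical Analyses section of the protocol article states: "A Poisson regression will be used to estimate differences between groups for postoperative outcomes (ie, length of hospital stays, postoperative complications". The bracketed list, opened by an 'ie', is closed by two further items, emergency department return and death. It names no other model family, dispersion check or robust variance for these outcomes. The same paragraph states that "An α of .05 will be considered statistically significant".

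The Outcome Measures section describes the outcomes. Mortality is assessed at 90 days, so each patient either has the event or does not. Emergency department return is assessed over the same 90 days, while Table 3 lists the item as visits, in the plural. For complications, "The severity of complications will be graded according to the Clavien-Dindo classification"; the article does not say whether the analysed response is the number of complications, any versus none, or the grade.

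The planned groups are "32 in the program and 32 who decline" (Participants section). Feasibility is the primary outcome, and the postoperative outcomes are secondary.

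**The concern.** An ordinary Poisson regression takes its standard errors from the assumption that the variance equals the mean. That assumption fails in different ways for the listed outcomes.

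- **Length of stay.** If the variance exceeds the mean, the standard errors are too small. Pooling lung and esophageal resections makes this plausible, and the Introduction itself says that complications lengthen stay.
- **Yes/no outcomes.** The true variance is p(1 − p), below the Poisson value of p, so the standard errors are too large.
- **Rare outcomes.** A group with no events gives a rate ratio of zero or infinity, or an undefined one if both groups are empty. Changing the variance estimator does not help.

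The Discussion counts it as a strength that the standard-of-care comparator yields preliminary effect estimates. An apparent difference in stay, judged at a nominal 5% but carrying a much larger real error rate, would weaken that use.

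**Working it through.** **Group size.** The Participants section takes 10 surgical patients a month over 16 months, with 25% enrolling and 20% lost to attrition. So 10 × 16 × 0.25 = 40 enrolled, and 40 × (1 − 0.20) = 32. The figure reproduces. I use 32 per group, and α = 0.05 taken as two-sided; the article does not state sidedness, but it uses 95% CIs.

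**Length of stay.** The article gives no mean or SD, so the values below are assumptions. With dispersion φ = SD²/mean, the Poisson standard error of the log rate ratio is too small by √φ. Actual coverage of a 95% interval is 2Φ(1.96/√φ) − 1, whatever the group size. For mean 5 and SD 3: φ = 9/5 = 1.8, √φ = 1.34, 1.96/1.34 = 1.46, coverage 86%. The last column is the rejection rate in 20,000 simulated null trials of 32 versus 32 (negative binomial data; Poisson data in the first row).

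| Mean/SD (days) | φ | √φ | Coverage | Type I error, formula | Type I error, simulated |
|---|---|---|---|---|---|
| 5/2.24 | 1.0 | 1.00 | 95% | 5% | 5.1% |
| 5/3 | 1.8 | 1.34 | 86% | 14% | 14.0% |
| 5/4 | 3.2 | 1.79 | 73% | 27% | 27.7% |
| 7/5 | 3.6 | 1.89 | 70% | 30% | 30.2% |
| 5/5 | 5.0 | 2.24 | 62% | 38% | 37.6% |
| 7/7 | 7.0 | 2.65 | 54% | 46% | 45.3% |

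Pooling alone can create overdispersion. Suppose stay were exactly Poisson within each operation, with assumed means of 4 and 10 days in an 80/20 mix. The pooled mean is 0.8 × 4 + 0.2 × 10 = 5.2. The variance is 5.2 + 0.8 × 0.2 × 6² = 10.96, so φ = 2.1 and type I error is about 18%, before any patient-level spread.

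In the same simulations, a dispersion-scaled (quasi-Poisson) standard error gave type I error of 4.7% to 5.2%, and a robust-type standard error gave 5.8% to 6.4%.

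**Mortality.** The only risks in the article are 30-day figures of up to 2.8% and 10%, used here as a proxy for 90 days. Expected deaths per group are 32 × 0.028 = 0.9 and 32 × 0.10 = 3.2. The chance that at least one group has none is 1 − [1 − (1 − p)³²]²:
- p = 2.8%: (0.972)³² = 0.403, giving 1 − 0.597² = 64%
- p = 5% (assumed midpoint): (0.95)³² = 0.194, giving 35%
- p = 10%: (0.90)³² = 0.034, giving 7%

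As an illustration, a Poisson fit to 0 versus 2 deaths in 32 versus 32 returned a log rate ratio of 20.4 with a standard error of about 11,459.

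**Any/none outcomes.** The Poisson standard error of the log risk ratio is too large by 1/√(1 − p): 1.4% at p = 2.8%, 5% at 10%, 12% at 20%, 20% at 30% and 41% at 50%. The article gives no rate for complications or emergency returns, so the last three values are assumptions.

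**The case against.** The strongest reply is that the sentence says only Poisson regression. It neither states nor excludes a robust or scaled variance, and Poisson regression with robust errors is an accepted route to risk ratios. A condensed article may leave the variance estimator to an analysis plan that is not shown. This stands in part: for stay, and for any/none complications or emergency returns, the existing sentence could be carried out acceptably. It does not cover mortality, where an empty group defeats the regression under any variance. Nor does it alter the fact that one model is assigned by name to outcomes of different types.

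A reader might also infer several stronger things that the documents do not support:

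- **That the stay intervals are certainly far too narrow.** No SD is given, and the error vanishes when the SD is about the square root of the mean.
- **That a false finding of shorter stay is likely.** The 14% to 45% is two-sided. Under no true difference about half of those rejections, roughly 7% to 23%, would favour the program.
- **That the mortality intervals are seriously too wide.** At 2.8% to 10% the excess is 1% to 5%; the mortality problem is empty groups.
- **That emergency return is yes/no and complications are ordinal.** Both could be analysed as counts; only mortality is clearly binary.
- **That these estimates will size the next trial.** The article ties future sample-size work to physical function and patient-reported outcomes.
- **That the comparison group supplies nothing else.** Enrollment and Assessment describes clinical fitness and lung function tests for every potential participant.

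**Conclusion.** The point holds as a should-fix on secondary outcomes. It does not touch the feasibility targets, and the article already acknowledges that the nonrandomized design may decrease internal validity.

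For length of stay, the loss of coverage is material under plausible overdispersion. Its size rests on assumed means and SDs and on ordinary model-based standard errors being used. For mortality, the empty-group risk rests on 30-day figures standing in for 90-day risk and on 32 analysed per group. Ninety-day mortality cannot be lower than 30-day mortality in the same patients, but the printed risks are described as upper values, so the true chance could lie on either side of the range shown. The excess width for complications and emergency returns arises only if they are analysed as any/none.

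**What to change.** Replace the single sentence with one paragraph that states the response and the model for each outcome:

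- **Length of stay:** negative binomial regression, or Poisson regression with quasi-likelihood or robust standard errors.
- **Complications and emergency department return:** state whether each is any/none or a count. For any/none, use Poisson regression with robust variance and report risk ratios. For counts, use a count model that allows for overdispersion.
- **Clavien-Dindo grade, if it is the response:** an ordinal model for the highest grade, or a prespecified dichotomy.
- **90-day mortality:** number of deaths per group with exact 95% confidence intervals, and no regression. With 0 of 32 deaths, for example, the exact upper limit is 1 − 0.025^(1/32) = 10.9%, which is reportable where a rate ratio is not.

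This needs no new data or patients, only standard functions in R, which the plan already uses. The cost is a wider length-of-stay interval: by a factor of 1.3 to 2.6 on the log scale over the 5/3 to 7/7 range.
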